#### Data analysis

Routine data extracted from the MIS will be first analysed descriptively, with OASI rates, caesarean birth rates, episiotomy rates and OASI-CB use calculated for all eligible women pre and post implementation and by study arms. Because units in the sustainability arm have already implemented the OASI-CB as part of OASI1, effectiveness outcomes in these units will be analysed differently than in the two C-RCT arms.

For the C-RCT arms, multilevel logistic regression and estimation of adjusted odds ratios (aOR) will be used to assess the impact of the OASI-CB and the relative differences in the odds of OASI in the two C-RCT arms. The regression model will include a random effect to account for clustering at unit level, secular trends and individual case-mix factors (e.g. maternal age, ethnicity, BMI, parity, mode of birth and birthweight).

For the sustainability arm, OASI rates will be analysed longitudinally from the baseline period of OASI1 to end of OASI2, to ascertain the trends and the rate of change by various implementation strategies. The four specific time periods will include baseline (pre-OASI1), OASI1 implementation, post-OASI1 with no external support and OASI2. We will use multilevel logistic regression with random effects and case-mix adjustment as in the C-RCT arms, to estimate adjusted odds ratios (aOR) for each time period and to test the significance of the relative impact of OASI1 implementation as compared with OASI2 implementation to assess the effectiveness of additional “sustainability” strategies.

For all study arms, subgroup analyses of the effect of the care bundle on OASI rates will be carried out according to mode of birth (spontaneous or assisted) and parity. The Wald test will be used to test for significance of interaction terms.

The analysis will be done following intention-to-treat principle, with births analysed according to whether they took place during the baseline or implementation periods, irrespective of whether or not all aspects of the care bundle could be implemented.

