#### Sample size and power

The sample size calculation aimed to identify the minimum number of clusters (maternity units) required to provide a study power of at least 0.80 with a statistical significance level of 0.05 to detect a 0.5% difference in OASI rates between the peer support and lean implementation arms following the implementation of OASI-CB.

The OASI rate is 3.5% according to the National Maternity and Perinatal Audit (NMPA) [5]. The units in the peer-support arm are expected to achieve a similar rate of reduction in OASI rates as the relative reduction of 20% observed in OASI1, or in absolute terms a reduction in OASI rates from 3.5% to 2.8%. We assume that the relative reduction in the lean implementation arm will be only 5%, or in absolute terms a reduction in OASI rates from 3.5% to 3.3%.

Using the Shiny CRT Calculator [26] by Hemming et al. and a trial design that includes baseline measures, a cross-sectional sampling, an exchangeable correlation structure, a cluster size of 3600 (average maternity unit size according to NMPA), allowance for a varying cluster sizes (coefficient of variation 0.4 according to the NMPA), and an intraclass correlation of 0.007 (according to OASI1), the minimum number of clusters would detect the assumed difference in OASI after implementation of the OASI-CB is ten; therefore, the study will have ten units in each trial arm.

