#### Contextual survey

A contextual survey will complement subsequent analyses and evaluations of OASI-CB implementation at the unit and study arm levels to determine how maternity unit context impacts care bundle implementation. The survey will assess factors identified as significant to implementation OASI1 (i.e. number of staff, number of students, level of research activity) as well as the impact of the COVID-19 pandemic. Each unit’s maternity governance team will complete this survey, administered online, at project start.

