### Synthesis of clinical effectiveness and implementation data

If compliance (clinicians’ use of the OASI-CB) and survey data are of sufficient completeness and quality, this unit level data will be added to multivariate regression models with effectiveness data to identify and estimate any relationship between OASI rates and levels of OASI-CB adoption as well as any secondary implementation outcomes. For the two C-RCT arms, the regression analysis will assess the impact of care bundle adoption (based on NoMAD score from clinicians’ survey) on relative differences of odds of OASI. In the sustainability arm, the regression analysis will assess the impact of additional ‘sustainability strategies’ on the adoption of the care bundle and on odds of OASI.

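### The peer-versus-lean model and the power calculation both leave out unit-specific change between the two years; if such change exists, standard errors are too small and 80% power is optimistic

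*Protocol article*

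**What the plan says.** Data analysis describes a multilevel logistic regression for the C-RCT arms: "The regression model will include a random effect to account for clustering at unit level, secular trends and individual case-mix factors". Births are classed by whether they fell in the baseline or the implementation period. Study hypotheses states the primary effectiveness question as a difference between arms in the reduction of OASI rates.

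Sample size and power asks for a power of "at least 0.80 with a statistical significance level of 0.05 to detect a 0.5% difference in OASI rates" between the arms (3.3% lean, 2.8% peer support). It assumes "a trial design that includes baseline measures, a cross-sectional sampling, an exchangeable correlation structure", 3600 births per cluster, a coefficient of variation of cluster size of 0.4 and an ICC of 0.007, and arrives at ten units per arm.

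Elsewhere the article treats units as likely to differ in how far the bundle takes hold. The PARIHS section says that the favourability of context will affect implementation. The contextual survey is meant to "determine how maternity unit context impacts care bundle implementation", and it also covers COVID-19. The synthesis section plans, data quality permitting, to "identify and estimate any relationship between OASI rates and levels of OASI-CB adoption".

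**The concern.** In a comparison of changes, a random intercept removes the stable differences between units. What remains as error in such a model is essentially binomial noise over thousands of births per unit. That is the right error only if every unit in an arm has the same true change on the log-odds scale. An exchangeable structure says the same thing: two births in one unit are as strongly correlated a year apart as within a year (CAC = 1).

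Randomisation is by unit. If true change varies between units, that variation across 20 units belongs in the standard error, and more births per unit will not reduce it. Leaving it out makes confidence intervals for the peer-versus-lean odds ratio too narrow and p-values too small. The article wants this comparison to inform national scale-up, so a spurious advantage for peer support would be costly.

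**Working it through.** **Inputs from Sample size and power:** rates 3.3% and 2.8%; ρ = 0.007; m = 3600; CV 0.4; k = 10 units per arm; α = 0.05, taken as two-sided. **Assumed, because the documents do not give it:** the CAC.

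**1. Reproduce the stated design.** Take cluster-period means with a period effect and equal expected baseline rates.
- σ² = 0.0305 × 0.9695 = 0.02957
- Variance of a unit's period mean: V = ρσ² + (1−ρ)σ²/m = 0.00020699 + 0.00000816 = 0.00021514
- Correlation of a unit's two means: r = CAC × ρσ²/V = 0.962 × CAC
- Variance of the effect: (2/k) × V × (1−r²)

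At CAC = 1: 0.2 × 0.00021514 × 0.0744 = 3.20 × 10⁻⁶, so SE = 0.00179. Power = Φ(0.005/0.00179 − 1.96) = 79.8%. Using 3.325% (exactly 5% off 3.5%) gives 83.4%. The stated ten units per arm therefore reproduce, with 3600 births per period. If 3600 were the total over both periods (1800 each), power would be 51%.

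**2. Let the CAC fall to 0.95 (worked example, equal unit sizes first).**
- Correctly modelled: r = 0.914, 1−r² = 0.1646, SE = 0.00266, power 46.8%. With CV 0.4 it is 45.3%.
- Exchangeable model still fitted, with r₁ = 0.962: (true SE / model SE)² = (1 + r₁² − 2r₁r)/(1 − r₁²) = 0.1669/0.0744 = 2.244.
- That model weights units by size, so the excess is multiplied by 1 + CV² = 1.16: 1 + 1.16 × 1.244 = 2.443, a ratio of 1.56.
- Type I error = 2[1 − Φ(1.96/1.56)] = 21%.

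**3. Range of assumed CACs** (ρ = 0.007, 3600 per period, CV 0.4):

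| CAC | True SE / model SE | Type I error, random intercept only | Power if modelled correctly, 10 per arm | Units per arm for 80% |
|---|---|---|---|---|
| 1.00 | 1.00 | 5.0% | 79.8% | 11 |
| 0.99 | 1.14 | 8.4% | 69.5% | 13 |
| 0.98 | 1.26 | 11.9% | 61.3% | 16 |
| 0.95 | 1.56 | 21.0% | 45.3% | 24 |
| 0.90 | 1.97 | 32.0% | 32.2% | 35 |
| 0.80 | 2.60 | 45.1% | 21.8% | 57 |

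**4. Check by simulation.** Random-intercept logistic mixed models with a Wald test of arm by period were fitted to 400 simulated trials of 20 units per scenario, with no arm effect. Rejection rates were 4.3%, 11%, 21.5%, 32% and 46% at CAC 1, 0.98, 0.95, 0.90 and 0.80. A t test on unit-level changes in log odds stayed at 4–5%.

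**5. What a CAC of 0.95 means.** The SD of true unit change is √(2 × 0.05 × 0.00020699) = 0.45 percentage points, against a between-unit SD of √0.00020699 = 1.44. The plan's own expected reductions are 0.7 points (peer support) and 0.2 points (lean).

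**6. Where the effect is smaller.**
- With 1800 births per period, type I error is 6.7%, 8.4%, 13.4%, 20.7% and 31.7% for CAC 0.99, 0.98, 0.95, 0.90 and 0.80. The women's survey section implies a value in between: 8000/0.30 = 26,667 vaginal births in 4 months over 30 units, or about 2,667 per unit per year.
- If 0.007 is a logit-scale ICC, the unit variance is (0.007/0.993) × π²/3 = 0.0232. On the proportion scale, ρ ≈ 0.0338 × 0.0232 = 0.0008. With 3600 per period, type I error is then 6.6%, 8.3% and 11.6% for CAC 0.95, 0.90 and 0.80.

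Neither case-mix adjustment nor the matched pairs were modelled.

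**The case against.** The strongest reply is that a two-sentence model description in a condensed article does not fix the whole random structure. The model is said to include a unit-level effect, not to be confined to one. The paragraph on the sustainability arm speaks of random effects in the plural and likens its model to that of the C-RCT arms. An unseen SAP may add a unit-by-period term and a small-sample rule. This stands to the extent that the article's silence on degrees of freedom is not itself a fault. It does not remove the point. The one clustering term named is at unit level, the plural names no further term, and a secular trend, read naturally as common to all units, cannot absorb unit-specific change. The exchangeable structure in the power calculation is an explicit choice.

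A second reply is that the false-positive rate depends wholly on an unsourced CAC. That is right. A reader might infer that the planned test has a type I error several times 5%. The documents do not support that as a fact: inflation is nil at CAC 1, about 1.7 times nominal at 0.99 and 2.4 times at 0.98. It is also modest if the ICC is on the logit scale, and case-mix adjustment might absorb some unit-specific change.

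Third, a reader might infer that the plan contradicts itself. That too is more than the text bears. The context survey and the adoption analysis are exploratory, and neither asserts that OASI rates will change differently by unit. They do make identical change in every unit of an arm an uncomfortable assumption.

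**Conclusion.** The point holds in conditional form. As written, both the C-RCT model and the power calculation set unit-specific change between years to zero, in a unit-randomised comparison of changes. The direction is certain: any CAC below 1 makes the standard error of the peer-versus-lean contrast too small and the 80% power optimistic. The size is not certain. With the protocol's ICC on the proportion scale and 3600 births per period, type I error runs from 5% at CAC 1 to 45% at CAC 0.80, and correctly modelled power from about 80% to 22%. The reading on the proportion scale is reasonable because the protocol enters 0.007 directly into a calculation on rates, but its source cannot be checked here.

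**What to change.** - **Analysis.** Specify the primary test as the arm-by-period term in a logistic mixed model with a random unit effect and a random unit-by-period effect. Study participants describes randomisation within ten pairs, so the small-sample inference should respect them. Options are degrees of freedom based on units and pairs, or a permutation test that swaps allocation within pairs (2¹⁰ = 1,024 arrangements). Analysing unit-level changes within pairs is a simpler alternative.
- **Sample size section.** Say that 80% power holds only at CAC 1, show power for CACs of about 0.8 to 1, and state the scale of the ICC and that 3600 is per period.
- **Timing.** Settle this before outcome data are analysed.

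**Cost.** Changes of wording and slightly more model fitting; no extra data. Intervals become wider and the stated power falls. Even at CAC 1, a t reference on 18 degrees of freedom (pairs ignored) gives 75% instead of 80%.

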### Implementation evaluation

Four surveys will be used to collect unit-level data: a contextual assessment survey, an Implementation Process Survey for OASI QI Leads, a clinicians’ survey, and a postnatal survey for women. Qualitative methods in the form of activity logs and focus group discussions will also be used. Timing of data collection activities are outlined in Fig. 6.

**Fig. 6 Fig6:**
[figure not shown]
OASI2 study timeline

#### Contextual survey

A contextual survey will complement subsequent analyses and evaluations of OASI-CB implementation at the unit and study arm levels to determine how maternity unit context impacts care bundle implementation. The survey will assess factors identified as significant to implementation OASI1 (i.e. number of staff, number of students, level of research activity) as well as the impact of the COVID-19 pandemic. Each unit’s maternity governance team will complete this survey, administered online, at project start.

#### Implementation process survey with OASI QI Leads

OASI QI Leads will be surveyed at two points during the study: during the first and last three months of the implementation period. These surveys focus on the facilitation model and will measure perceptions of the expert outreach support received by the sustainability arm units, the peer support model or the lean implementation model. These surveys include the previously developed acceptability of intervention measure (AIM), intervention appropriateness measure (IAM) and the feasibility of intervention measure (FIM) [27]. Both OASI QI Leads for all 30 participating units will be invited to complete the survey.

#### Clinicians’ survey

Midwives and obstetricians from participating units will be invited to complete a survey in the first and last three months of the implementation period that will measure:
Adoption of the OASI-CBPerceptions of the OASI-CBPerceptions of the implementation strategiesParticipation in implementation strategies

The AIM, IAM and FIM are used as in the survey with OASI QI Leads. Adoption is measured using the Normalization Measurement Development (NoMAD) Tool [28], developed in line with constructs of the Normalization Process Theory, which focuses on the work done at an individual level by adopters of new practices. All midwives and obstetricians will be invited to participate by way of a census method.

#### Women’s postnatal surveys

Women who give birth in participating units will be surveyed about their experiences with the OASI-CB. Survey questions have been extensively reviewed by patient and public involvement (PPI) groups for sensitivity. Over a 4-month period, all women who had a live vaginal birth will be invited to participate in the survey by way of a census method. An attending clinician will approach eligible women at an appropriate time after birth and before discharge from the hospital to explain the survey and provide a participant information sheet and consent form. Participants will receive a link to the online survey via e-mail 2 weeks after the birth of their baby and up to three reminders thereafter if the survey has not yet been completed. Assuming a 30% response rate [29, 30], an estimated 8000 surveys will be completed, which is adequate for descriptive analyses (no comparators for these survey data).

#### Survey data analysis

All survey data will be aggregated for each assessed implementation outcome. For previously validated scales (e.g. AIM, IAM, FIM, NoMAD) internal consistency will be first calculated (Cronbach’s alpha coefficients). Assuming acceptable reliability (Cronbach’s alpha of 0.70 or higher), item ratings will be aggregated into scale scores.

Multivariate regression analyses with clinicians’ survey data will explore the relationship between favourable care bundle perceptions and high care bundle adoption (outcomes) and implementation strategies used and facilitation model assigned to the study arm (predictors). Analyses will also explore the impact of contextual factors (size and type of unit, prevalence of students, staff turnover rates).

Results from the OASI QI Leads’ and clinicians’ surveys from the two time points will be compared within units to assess rating/score variation over time.

Fidelity assessment will be carried out as follows: OASI QI Leads’ survey data for each outcome will be compared with clinicians’ awareness of, participation in and perceptions of the discrete implementation strategies used in unit from the clinicians’ survey. Clinicians’ awareness of strategies in their unit serves as a proxy indicator of OASI QI Leads’ fidelity to the prescribed implementation strategies. Clinicians’ participation in and perceptions of the strategies will be taken as indicators of the clinicians’ fidelity to engagement with the strategies.

Women’s postnatal survey data will be analysed descriptively by each of the OASI-CB components and will be compared between units within study arms. No specific hypotheses will be tested in relation to this dataset.

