**Fig. 4 Fig4:**
[figure not shown]
OASI2 logic model developed using implementation mapping

The logic model takes into account the determinants of implementation success as defined by the PARIHS framework, which defines four core ‘determinants’ of implementation success: innovation, context, recipients, and facilitation [18]. ‘Facilitation’ refers to the OASI QI Leads leading implementation and acting as facilitators. ‘Recipients’ are the clinicians ‘receiving’ the implementation and adopting the care bundle into their routine practice. Facilitation and recipients are therefore internal determinants of implementation success. Conversely, ‘innovation’ and ‘context’ are external determinants that may impact the OASI QI Leads and clinicians. Innovation refers to the acceptability and evidence base supporting the four components and the OASI-CB as a whole; depending on the strength of this evidence, this can have a positive or negative impact on OASI QI Leads, clinicians, and ultimately, the implementation. The favourability of the context will further impact implementation. At the national level, this depends on the opinion of professional clinical leadership and support of women’s advocacy groups; a favourable local context includes existing capacity for quality improvement and senior buy-in early in the implementation period. Context also takes into account the approval and support of the care bundle’s target population; women who are eligible to receive the care bundle and women who have received it.

The PARIHS framework considers facilitation to be the “active ingredient” of implementation, acknowledging that facilitator(s) of change in clinical practice may be internal or external and focus on enabling others to make changes [21]. Each of the three study arms are defined by a set of implementation strategies that are influenced by the facilitators involved in the implementation:
The lean units will rely on their local OASI QI Leads;The peer support units have their local leads + the support of experienced buddy leads from nearby units; andSustainability units have their local leads + centralised support from the Project Team.

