#### Peer support (C-RCT arm 1) implementation strategies

The ten units randomised to this study arm are paired with units from the sustainability arm. The OASI QI Leads in this arm will receive the Implementation Toolkit and benefit further from continuous external support from the sustainability arm, their buddy facilitators. OASI QI Leads in the peer support arm will maintain monthly contact with their buddy facilitators. Continuous peer support is the defining feature of this scale-up method that distinguishes it from lean implementation (see below).

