**Fig. 5 Fig5:**
[figure not shown]
Three-level ‘iceberg model’ with study outcomes and data sources

The Proctor et al. implementation outcome taxonomy [19] guides our evaluation of several implementation outcomes across the three levels shown in Fig. 5. The implementation outcomes are either perception-based or action-based. Acceptability (Is it agreeable, palatable, satisfactory?), appropriateness (Is it compatible?) and feasibility (Is there capacity to do this?) are evaluated based on how an evidence-based intervention (EBI) and/or its implementation are *perceived*. Adoption of the EBI, fidelity (Is the EBI/its implementation carried out as intended?), the EBI’s coverage of the target population and sustainability are evaluated based on *actions taken* or behaviours changed.

The facilitation model is assessed based on how facilitators perceive its acceptability and appropriateness and feasibility.

Implementation strategies are assessed based on whether facilitators deliver the strategies as intended, whether clinicians engage or participate in the strategies as expected (fidelity to the delivery of and engagement with the strategies), and how clinicians perceive their acceptability and appropriateness.

The OASI-CB is assessed in terms of how clinicians perceive its acceptability, appropriateness and feasibility, and whether clinicians adopt the care bundle with fidelity (as intended) into their routine practice and offer it at high coverage. The primary implementation outcome (adoption) and clinical effectiveness outcome (OASI rate) are both measured at this level.

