#### Study hypotheses

There are two hypotheses, one related to the primary clinical effectiveness outcome (OASI rates) and one to the primary implementation outcome (OASI-CB adoption):
The OASI rate will decrease in all study arms following the implementation of OASI-CB. There will be a significant difference in reduction of OASI rates between units in the peer support and lean implementation arms, such that the reduction in OASI rates will be higher in the peer support arm as compared with the reduction in OASI rates in the lean implementation arm.There will be a significant difference in care bundle adoption between units in the peer support and lean implementation arms, such that the levels of adoption will be higher in the peer support arm.

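### The only stated analysis relating adoption to study arm lists strategies used beside the assigned facilitation model; entered together, they do not give the peer-versus-lean difference in Hypothesis 2

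*Protocol article*

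**What the plan says.** **Hypothesis.** Under Study hypotheses, the second hypothesis reads: "There will be a significant difference in care bundle adoption between units in the peer support and lean implementation arms", with the higher level expected under peer support. Evaluation framework and study outcomes gives adoption its status: "The primary implementation outcome (adoption) and clinical effectiveness outcome (OASI rate) are both measured at this level". The Abstract also says that the two randomised arms will be compared on adoption.

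**Analysis.** Survey data analysis states: "Multivariate regression analyses with clinicians’ survey data will explore the relationship between favourable care bundle perceptions and high care bundle adoption (outcomes". The predictors follow in the same sentence: "implementation strategies used and facilitation model assigned to the study arm (predictors". Contextual factors are explored as well. No other analysis in the article has adoption as outcome and arm as predictor.

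**Strategies and arms.** The section on implementation mapping and PARIHS says: "Each of the three study arms are defined by a set of implementation strategies". The peer support section adds: "Continuous peer support is the defining feature of this scale-up method that distinguishes it from lean implementation".

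**Clustering.** For the clinical outcome, Data analysis states: "The regression model will include a random effect to account for clustering at unit level". Survey data analysis has no matching statement. Implementation evaluation opens with: "Four surveys will be used to collect unit-level data".

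**The concern.** Hypothesis 2 asks what allocation to peer support does to adoption by whatever route, which is a total effect. Part of that effect is expected to run through the strategies that buddies help the local leads to deliver. A model that holds strategies used constant asks a different question: what does allocation do beyond its effect on strategies? The better peer support works through strategies, the smaller the answer. The trial could then report no arm difference on its primary implementation outcome although one exists.

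A second, conditional worry is precision. NoMAD is answered by individual clinicians, but units are randomised. If clinicians were analysed as independent, the p-value for arm would rest on the wrong sample size.

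**Working it through.** **1. The plan's own figure.** The article gives no sample size, power, ICC or respondent count for adoption, so there is no adoption figure to reproduce. Its ten units per arm is for the OASI rate. With 3.3% versus 2.8%, 3600 births per unit and period, a baseline period, ICC 0.007, size variation 0.4 and two-sided 0.05, ten units per arm give power 0.793, or 0.827 with the unrounded 3.325%. The stated 0.80 reproduces within rounding but says nothing about adoption.

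**2. Is there another arm analysis of adoption?** Going through the article:
- The two survey time points are compared within units, not between arms.
- The fidelity assessment compares leads' and clinicians' reports; it does not test arms.
- For the randomised arms, the synthesis section uses adoption to predict OASI, not as an outcome.

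That leaves the regression under Survey data analysis.

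**3. What can strategies used mean?** In Table 2, lean and peer support share two rows (selection of leads, Toolkit). They differ in two: pairing with buddies, and monthly buddy contact. The remaining rows belong to the sustainability arm.
- If the variable records buddy pairing and contact, it restates allocation.
- If it records activities delivered or attended, as in the clinicians' survey and activity logs, it is measured after randomisation and lies on the path from arm to adoption.

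In neither case does the adjusted arm coefficient equal the total difference.

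**4. Size of the distortion (assumed inputs).** In a linear model, total effect = direct effect + effect through strategies. Adjusting for strategies leaves the direct part, and even that only if nothing else drives both strategies and adoption. For an assumed total of 0.30 SD:
- Half through strategies: 0.30 × (1 − 0.5) = 0.15.
- All through strategies: 0.30 × (1 − 1) = 0.

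A simulation (10 versus 10 units, 40 clinicians per unit, SD 1, 2000 runs) gave adjusted coefficients averaging 0.14 to 0.15 and about 0.00. A plain comparison of unit means by arm recovered about 0.30 in every case.

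**5. Clustering, if ignored (assumed inputs).** Design effect DE = 1 + (m − 1) × ICC. The standard error is too small by a factor √DE. Actual type I error = 2 × [1 − Φ(1.96/√DE)]. For m = 60 respondents per unit:

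| ICC | DE | √DE | Type I error |
|---|---|---|---|
| 0.02 | 1 + 59 × 0.02 = 2.18 | 1.48 | 0.18 |
| 0.05 | 1 + 59 × 0.05 = 3.95 | 1.99 | 0.32 |
| 0.10 | 1 + 59 × 0.10 = 6.90 | 2.63 | 0.46 |

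Over 20 to 100 respondents per unit and ICC 0.01 to 0.10, the range is 0.07 to 0.55. In the simulation with 40 per unit and no true effect, the model without a unit term rejected 15% (ICC 0.02) to 24% (ICC 0.05) of the time. The comparison of unit means rejected 5%.

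**The case against.** The strongest reply is that this regression is not offered as the test of Hypothesis 2. The text speaks of analyses in the plural, says they will explore relationships, and does not mention the hypothesis. One list of predictors does not fix a model formula, and a condensed article may leave the confirmatory model to a fuller document. Relating strategies to adoption is also a proper aim of a hybrid trial. All this stands as a limit on the claim: the text does not show that the team will test Hypothesis 2 this way. It does not remove the point. The one predictor set stated for adoption by arm does not answer the hypothesis, and an SAP that followed it would carry the problem forward.

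A reader might infer two stronger things that the article does not support:
- **That arm and strategies are nearly collinear.** Most strategies are open to both randomised arms: all units receive the guidebook with its six key strategies, and clinicians report their own participation. Use can vary within arm, so near-collinearity would follow only if the variable were essentially buddy contact.
- **That the adoption model has no unit effect and therefore a wrong error term.** The section is silent; it does not exclude one. The clinical model shows that the authors account for clustering. The surveys are described as unit-level, both in the quoted sentence and in the synthesis section, and an analysis of unit means would need no unit term. On the other side, the regression is said to use clinicians' survey data, NoMAD concerns individual work, and the aggregation spelled out is of items into scale scores. The level of analysis is unclear rather than wrong.

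**Conclusion.** The point holds for the predictor set. Followed as written, with both predictors in one model, the only stated analysis of adoption by arm does not estimate the total peer-versus-lean difference in Hypothesis 2. The arm coefficient shrinks towards zero as more of the effect runs through strategies: halved if half does, zero if all does. The direction follows from the model. The amount depends on a mediated share that the article does not give, and the 0.30 SD is only an illustration.

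Clustering is a supporting point and conditional. Inflation of type I error to about 18% to 46% arises only if clinician-level responses are analysed without a unit term, at an assumed 60 respondents per unit and ICC 0.02 to 0.10. The article does not say that this will be done. Because adoption is a primary outcome, both matters should be settled in writing before the survey data are analysed.

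**What to change.** Name the test of Hypothesis 2 explicitly:
- Outcome: NoMAD score.
- Comparison: randomised arm, peer support versus lean only, leaving out the non-randomised sustainability arm.
- Covariates: no strategy variables taken up after randomisation. Contextual factors measured at project start may be added.
- Error: the unit as randomised cluster, by a unit random effect or by unit-level means, with degrees of freedom based on units rather than clinicians, and the ten randomised pairs taken into account. A paired analysis of unit means, for example, has 10 − 1 = 9 degrees of freedom.

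Keep the regression with strategies used as a secondary explanatory or mediation analysis. Label it so, and state that its arm coefficient is not the answer to Hypothesis 2. State also whether survey regressions use clinicians or unit summaries.

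The cost is a few sentences in the protocol or SAP and one additional model on data already planned for collection.
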